### Outcome measures

The assessment will be conducted on four time points, including at baseline, 2 weeks and 4 weeks after the beginning of the treatment, and 4 weeks after the end of the treatment (Table 1). All assessments will be performed by therapists who do not know the specific group.

**Table 1 T1:** SPIRIT figure.

	**Screening**	**Baseline**	**Intervention**			**Follow weeks**
Time Point	**-t** _ **2** _	**-t** _ **1** _	**0**	**w2**	**w4**	**4w**
Enrollment						
Informed consent	**√**					
Demographic information	**√**					
Medical history	**√**					
MMSE	**√**					
Eligibility assessment	**√**					
Random allocation		**√**				
Interventions						
Tui Na+TMS group						
Cnventional group						
Assessments						
Fugl-Meyer-UE		**√**		**√**	**√**	**√**
MS		**√**		**√**	**√**	**√**
MAS		**√**		**√**	**√**	**√**
MBI		**√**		**√**	**√**	**√**
MEP		**√**		**√**	**√**	**√**
fNIRS		**√**		**√**	**√**	**√**
Adverse event			**√**	**√**	**√**	**√**

Description of the protocol. -t2, first contact with participants; -t1, baseline evaluation;0, starting day of the treatment; w2, 2weeks after the start of treatment;w4, 4 weeks after the start of treatment and post evaluation;4w, 4 weeks after the end of treatment; MMSE, Mini-Mental State Examination; Fugl-Meyer-UE, Fugl-Meyer Upper Extremity Scale; MS, Muscle Strength; MAS, Modified Ashworth, MBI, Modified Barthel Index; MEP, Motor evoked potentials; fNIRS, functional near-infrared spectroscopy; The orange line represents the treatment time in the figure, with a total of 4 weeks of treatment.

### Primary outcome

#### Fugl-Meyer-UE assessment

The primary outcome measure is the Fugl-Meyer-UE Assessment (28). To evaluate the motor effects of rTMS synergized with Tui Na treatment on patients with stroke, we can also examine the changes in motor value provided by Fugl-Meyer-UE Assessment in patients. Fugl-Meyer Assessment is a method for evaluating sensorimotor disorders in stroke patients and is now widely used in the clinical evaluation of motor function. After many tests, Fugl-Meyer assessment scores have good consistency, responsiveness, and accuracy. Regarding UL motor function, the maximum Fugl-Meyer-UE score is 66, which is equivalent to the need for complete sensorimotor recovery.

### Secondary outcomes

#### Muscle strength and modified Ashworth assessment

Muscle Strength Assessment means the strength of muscle contraction during random exercise of the limb (29). The assessment is to instruct the patient to make the upper arm abduction, adduction, forearm extension and flexion, wrist extension and flexion, finger abduction, adduction, fist clenching and other movements, and observe whether the muscle strength is normal, decreased or paralyzed, and pay attention to the paralyzed site. Modified Ashworth Assessment is a method to check the tension of muscles in a state of rest and relaxation (30).

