Tui Na (Chinese massage therapy) is a relatively simple, inexpensive and non-invasive intervention, and has been used to treat stroke patients for many years in China. Tui Na mainly acts on specific parts of the body through manipulation, on the one hand, it plays a local therapeutic role in the body, on the other hand, it can also have a certain impact on various systems of the body through nerves, body fluids and other ways, so as to achieve the role of treating diseases (12). Clinical observation suggested that Tui Na might be a safe and effective treatment for post-stroke UL motor dysfunction (13, 14). Although the mechanism of Tui Na on treatment of post-stroke motor dysfunction is limited, some possible mechanism was proposed. Tui Na manipulation stretched the muscle–tendon complex and stimulate the Golgi tendon organ that could inhibit alpha motor neurons and reduce spasm (15). Tui Na manipulation might reinforce sensory stimulation and activate the gamma efferent fibers of muscle stretch receptors that make receptors more sensitive to stretch (15). Soreness and distension that was caused by Tui Na manipulation will excite the sensory cortex, thus inhibit reticular formation of brainstem and decrease the muscle tone (15). For more than two thousand years, traditional Chinese medicine therapists have been using Tui Na act on governor meridian-related acupoints to treat spinal-related diseases and many visceral disorders (16). The spine is the pillar of the human body and the medium that connects the brain and the peripheral organs. The spine is the pathway of the governor meridian in traditional Chinese medicine, which dominates people's life activities (17). The spine contains the spinal cord, with spinal nerves and sympathetic pathways on both sides. Although there are great differences in theory and technology between traditional Chinese and western medicine, they are almost the same in understanding the importance of the spine and preventing and treating diseases by adjusting the spine and its related surrounding tissues.

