### Inclusion criteria

People will be eligible for inclusion if they meet the following criteria: (1) First ever unilateral ischemic stroke diagnosed by imaging and the course of the disease ranged from 2 weeks to 6 months. (2) UL dysfunction as indicated by the Fugl-Meyer motor function score ≥20-40/66. (3) Aged 40–70 years, regardless of sex. (4) No severe cognitive or communication impairment as indicated by the Mini-mental state examination (MMSE) ≥ 24 points.

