#### Efficacy analysis

The data in accordance with normal distribution and homogeneity of variance in the main and secondary indicators will be compared with *t*-test to see if the difference between the two groups before and after treatment is statistically significant. The rank data with non-normal distribution or uneven variance will be analyzed by Wilcoxon rank sum test.

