## Discussion

According to the holism of traditional Chinese medicine, the human body is an organic whole, and the various components of the human body are inseparable in structure, coordinate and complement each other in function, and influence each other pathologically. Therefore, we adopt a holistic and local approach in Tui Na therapy, which not only regulates the local rehabilitation of the UL, but also pays attention to the overall condition of the patients. Similar to acupuncture (34), Tui Na on the hemiplegic UL can stimulate the peripheral nerves, and promote the activation and integration of the cortical sensorimotor network. Similar to physical therapy (35), Tui Na on the hemiplegic UL can coordinate the balance of muscle tension between muscle groups, inhibit and control spasm, and then establish a normal movement pattern. Tui Na on the spine region can promote the adjustment of the overall function of the body. All organs in the human body are stimulated by nerves. Tui Na can regulate the function of these organs by stimulating the autonomic nervous system and improve the pathological injury of the whole body after stroke, so as to provide a better internal environment for the recovery of brain and limbs (36).

In recent years, the development of Functional magnetic resonance imaging (fMRI), electroencephalography (EEG) and fNIRS has given impetus to the research of rehabilitation. Among them, fNIRS is an emerging neuroimaging technique that indirectly reflects the intensity of neural activity by detecting the changes in blood oxygen activity in the cerebral cortex (33). fNIRS has a good temporal resolution (sampling rate up to dozens of Hz) and spatial positioning ability (centimeter scale), as well as portability, economy and good ecological validity (37). In a review published in Nature in 2008, various brain imaging techniques were compared, and fNIRS was evaluated as “an interesting compromise that involves inexpensive and portable imaging techniques” in real-time brain imaging (38). These characteristics make fNIRS very suitable for clinical practice in stroke rehabilitation evaluation and rehabilitation intervention.

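### Modified Ashworth change is compared across the whole groups without conditioning on baseline grade, so patients at grade 0 dilute any tone-reduction effect by an amount the protocol does not let one fix

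*Protocol article*

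**What the plan says.** - **Outcome.** The section on muscle strength and modified Ashworth assessment describes the scale: "Modified Ashworth Assessment is a method to check the tension of muscles in a state of rest and relaxation". Table 1 schedules it at baseline, week 2, week 4 and follow-up.
- **Entry.** The motor criterion is "UL dysfunction as indicated by the Fugl-Meyer motor function score ≥20-40/66", and for time since stroke "the course of the disease ranged from 2 weeks to 6 months". No inclusion or exclusion criterion concerns muscle tone.
- **Expected direction.** The Background proposes that Tui Na may "thus inhibit reticular formation of brainstem and decrease the muscle tone". The Discussion says that it can "inhibit and control spasm".
- **Analysis.** The Efficacy analysis section applies one rule to all main and secondary indicators: a t-test of the before-after difference between the two groups if assumptions hold, and otherwise "The rank data with non-normal distribution or uneven variance will be analyzed by Wilcoxon rank sum test". The analysis sets are intention-to-treat and per-protocol.
- **Baseline adjustment.** Under Comparability analysis, a baseline variable becomes a covariate only if the groups differ on it significantly and in a way judged professionally relevant. MAS is not among the variables named there, although the list is worded as open.

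**The concern.** MAS is the listed outcome that bears most directly on the proposed peripheral action of Tui Na. A patient at grade 0 has no tone to lose, so the change can only be nil or upward. In a patient who starts with raised tone, a fall can be seen. The planned test ranks or averages both kinds of change together.

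Two things follow. The average difference shrinks in proportion to the grade-0 share, and new tone in grade-0 patients adds variation unrelated to tone reduction. Baseline grade, which separates the two kinds of patient, enters the analysis only if it happens to differ significantly between arms. Allocation is by simple randomisation, so the grade-0 share can also differ between arms by chance without reaching that threshold. At stake are the sensitivity and reading of one secondary outcome. The primary Fugl-Meyer comparison is not affected.

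**Working it through.** **The plan's own figure.** The only sample-size figure concerns Fugl-Meyer change: (1.960 + 0.842)² × 2.0² × 2 / (6.6 − 2.3 − 3)² = 37.17, rounded up to the stated 38 per group. It reproduces, but says nothing about MAS. The protocol gives no MAS effect, SD or grade-0 share, so everything below rests on assumptions.

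**Mean difference.** Assume one grade per patient. In raised-tone patients, let a one-grade fall occur in 55% (experimental) v 25% (control), and a one-grade rise in 10% of both arms. The difference in these patients is −(0.55 − 0.25) = −0.30. Let f be the grade-0 share, and e_T and e_C the rates of new tone among grade-0 patients in the experimental and control arms. Then

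D = (1 − f)(−0.30) + f(e_T − e_C).

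With equal new tone in both arms:
- f = 0.2: 0.8 × −0.30 = −0.24
- f = 0.4: 0.6 × −0.30 = −0.18
- f = 0.6: 0.4 × −0.30 = −0.12

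**Power of the planned rank-sum test.** Simulated with 45 per arm, two-sided 5%, and new tone in 10% to 40% of grade-0 patients, equal in both arms:

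| Grade-0 share | Difference | All patients | Baseline MAS ≥ 1 only |
|---|---|---|---|
| 0% | −0.30 | 70% | 70% |
| 20% | −0.24 | 55-47% | 60-62% |
| 40% | −0.18 | 34-23% | 46-48% |
| 60% | −0.12 | 22-13% | 32-35% |

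At a grade-0 share of 5-10% the loss is small: the subset gains only about 2 to 8 points.

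**Cross-check on a continuous scale.** Take 38 per arm, d = 0.65 SD in raised-tone patients and p = 1 − f. If grade-0 patients do not change at all, the variances are p(1 + d²) − (pd)² and p, and power = Φ(pd/SE − 1.96). At p = 0.6: SE = √((0.7014 + 0.6)/38) = 0.185, and 0.39/0.185 − 1.96 = 0.15, so power is 56%. For p = 0.8, 0.6 and 0.4, power is 70%, 56% and 39%. It is 62%, 40% and 20% if grade-0 patients vary as much as the rest. The raised-tone subset gives 72%, 59% and 43%. With p = 1, power is 81%.

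**Unequal new tone.** The direction of any arm difference in new tone decides what pooling does:
- More in the experimental arm (50% v 30%), f = 0.4: D = −0.18 + 0.4 × 0.20 = −0.10, power 12-13%.
- Less in the experimental arm (20% v 40%), f = 0.4: D = −0.18 − 0.08 = −0.26. Power is 50% in all patients and 47% in the subset.
- The same rates, f = 0.6: D = −0.12 − 0.12 = −0.24. Power is 46-48% in all patients and 33-36% in the subset, across two runs.

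**Excess needed to cancel the effect.** D = 0 when e_T − e_C = 0.30(1 − f)/f. This is 1.20 at f = 0.2 (impossible), 0.45 at f = 0.4 and 0.20 at f = 0.6.

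**Conditioning on baseline grade in all patients.** A rank-sum test stratified by baseline grade matched or beat the unstratified test, within simulation error, in every setting tried. In three settings at f = 0.4 its power was 39% v 34%, 31% v 26% and 64% v 51%.

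**The case against.** The strongest reply is that nothing here is invalid. Comparing a secondary outcome in all randomised patients follows from intention-to-treat, and a baseline-tone subset is detail that a separate analysis plan could hold. Tone reduction is also not the trial hypothesis, which concerns upper-limb motor function and sensorimotor cortex activity. All of this stands and limits the weight of the point. It does not remove it, because the protocol does fix the whole-group before-after comparison and a rule that admits baseline covariates only after a significant difference.

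A reader might go further and infer that new tone counts against Tui Na, that the result could point the wrong way, or that a null MAS result would mean nothing. The protocol does not support these readings. New tone is scored alike in both arms. At equal rates it adds noise, not bias. No passage suggests that tone appears more often with Tui Na, and the mechanisms it cites fit prevention of tone at least as well. In that case scoring new tone as worsening is correct. As for a null result, the raised-tone subset is itself underpowered, so it would be inconclusive there too.

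A reader might also conclude that the test should be confined to raised-tone patients. That helps when new tone is equal between arms, but discards real effect if Tui Na prevents new tone, as the 60% grade-0 example shows.

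Finally, treating each patient as having one grade is an assumption. If several muscle groups are scored, fewer patients sit at zero throughout.

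**Conclusion.** The point holds as a loss of sensitivity in one secondary outcome. Patients at grade 0 can enter, they cannot improve on MAS, and the planned comparison ignores baseline grade unless it differs significantly. Any tone-reduction effect is therefore diluted by the grade-0 share. Under the assumed rates the loss is minor at 5-10% grade 0 and substantial from about 20%. The true share is not in the protocol, so a hidden effect is possible but not shown. The between-arm comparison remains valid, and no bias against Tui Na is demonstrated.

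Much of the lost power reflects fewer patients who can respond, and no analysis restores it. Conditioning on baseline grade recovers part of it: about 5 points in two of the settings tried and 13 in the third.

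**What to change.** Leave entry and data collection unchanged, and amend the MAS analysis wording:

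1. Keep all randomised patients. Compare the week-4 MAS grade as an ordinal outcome conditional on baseline grade, for example with a proportional-odds model including baseline MAS or a rank-sum test stratified by baseline grade. Do this whether or not baseline MAS differs significantly between arms.
2. Beside this, not instead of it, prespecify a supportive comparison in patients with baseline MAS of at least 1. The subset is defined before treatment, so the randomised comparison is kept within it.
3. Report newly appearing tone by arm in patients at grade 0 at baseline.

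Baseline MAS is already scheduled in Table 1, so nothing new is collected. The cost is slightly more analysis work and low precision in the supportive subset.

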#### Modified barthel index assessment

Modified Barthel Index Assessment is a simple, reliable, sensitive and widely used method for evaluating activities of daily living. MBI is mainly used to assess the changes of independent living ability of stroke patients before and after treatment (31).

#### Motor evoked potentials

MEP is the muscle motor potential recorded by stimulating the motor cortex in the target muscle, and to examine the overall synchronization and integrity of the motor nerve transmission from the cortex to the muscle and the conduction pathway. TMS results in sequential activation of upper motor neurons, which in turn leads to spinal cord motor neuron activation, and is recorded by the surface Electromyography in the target muscle (32). In this research, at least 5 out of 10 monopulse stimuli will be given to the cortical representative region (M1) of the contralateral abductor pollicis brevis to induce MEP with an amplitude >50 μV as the motor threshold. The resting motor threshold (RMT) will be analyzed.

#### fNIRS

fNIRS will be used to record the time course of the functional plasticity of sensorimotor neural circuits during rTMS synergize with Tui Na intervention. At the time point of each evaluation, the task state and resting-state fNIRS brain imaging data of the patients will be recorded, and the cortical activity, functional connection plasticity and cortical lateralization will be calculated quantitatively (33). The fNIRS outcome measures, including Lateral Index, RSFC values and zfALFF values, will be specified in the section of fNIRS data analysis.

### Further outcome measurement

#### Adverse events

Further outcome measurements including the occurrence rate of headache, vertigo and hearing changes. Magnetic effects and strongly induced voltage during rTMS treatment may adversely affect implants in the brain or heart of patients, so patients with implants will be excluded when recruiting patients. Patients will be advised to remove magnetic objects such as necklaces, earrings and glasses during treatment to avoid safety incidents. Side effects such as headache, vertigo and hearing changes may occur during the treatment of rTMS. Once the above symptoms occur, the treatment will be stopped immediately to ensure safety. rTMS may induce epilepsy, the probability is very small, once it occurs, it will reduce the damage through the formulation of emergency treatment plan. In the process of Tui Na treatment, bone correction and other possible risk factors are not involved, and there is no serious risk.

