### Exclusion criteria

Exclusion criteria are as follows: (1) Patients with severe systemic diseases such as cardiovascular or pulmonary diseases who cannot tolerate rehabilitation treatment. (2) Patients diagnosed with mental illness such as severe depression, etc. (3) In addition to stroke, suffering from other neurological diseases such as Parkinson's disease and epilepsy, etc. (4) According to the safety guidelines, there are contraindications for TMS, such as metal foreign bodies or other electronic devices implanted in the body, etc. (5) Application of drugs that change the excitability of the cerebral cortex. (6) Patients with unstable or larger carotid plaques. (7) Patients with severe osteoporosis.

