### Research groups

Control group: conventional rehabilitation + rTMS.

The conventional rehabilitation treatments include physiotherapy therapy, occupational therapy and drug therapy. High-frequency rTMS will be used on the affected side of the primary motor cortex (M1).

Experimental group: conventional rehabilitation + rTMS + Tui Na.

In addition to the conventional rehabilitation treatment and high-frequency rTMS provided to the patients in the control group, the patients will receive Tui Na on the spine and hemiplegic side of UL.

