##### Selection-of-manipulations-and-operating-rules

Kneading, pressing, one-finger meditation and active joint manipulations will be selected. The standard manipulation requires the basic technical requirements of “lasting, powerful, uniform, soft and penetration.” “Lasting” means that the manipulation can be operated continuously for a certain period without interruption to maintain the consistency of movement and strength and to ensure that the amount of stimulation to the body accumulates to a certain extent. “Powerful” means that the manipulation must have a certain strength and reach a certain level. This kind of power is not brute force or violence but a skillful force that is used according to the different people and locations of treatment. “Uniform” means that the manipulation's strength, speed and operating range should be homogeneous, rather than sometimes light and sometimes heavy, sometimes fast and sometimes slow, and sometimes large and sometimes small. “Soft” refers to gentle and rhythmic movements, not stiff, rough, or brute force. “Penetration” means that the stimulation of the manipulation can reach the deep subcutaneous layer and viscera tissue. The above aspects are closely related and complement each other. The continuous use of manipulations can gradually reduce the muscle tension of patients so that the strength of manipulation can gradually infiltrate into the deep tissue. Uniform and coordinated movements can soften the manipulations. The combination of strength and skill makes the manipulation both powerful and soft.

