##### Procedure-of-treatment

The affected UL: the patients will be PLACED in a sitting position, and the therapist will focus on the acupoints from the hand to the shoulder to carry out kneading, pressing, one-finger meditation, and active joint manipulations. The appropriate force will be used to make the patient feel sore and distended, and the treatment time is about 15 min.

Spine: the patients will be placed in a prone position, and the therapist will focus on the acupoints from neck to waist to carry out kneading and pressing manipulations. Appropriate force will be used to make the patient feel sore and distended, and the treatment time is about 15 min.

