##### Matters-needing-attention-in-treatment

Treatments should be performed in a quiet room. The temperature and humidity should be appropriate. The therapist's hands should be kept clean and warm. Nails should be trimmed frequently so as not to cause discomfort to the patient or even damage the patient's skin. Fully communicate with patients to eliminate their nervousness. Closely observe the reaction of patients to timely adjust the amount of stimulation, and beware of adverse responses or accidents. In the event of an accident, the treatment should be stopped immediately.

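### The named safety rates cover only rTMS side effects shared by both arms; no Tui Na event is named, and the deliberately induced soreness has no place in the between-arm comparison

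*Protocol article*

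**What the plan says.** Under Further outcome measurement, Adverse events, the protocol article states: "Further outcome measurements including the occurrence rate of headache, vertigo and hearing changes". The same paragraph gives their source: "Side effects such as headache, vertigo and hearing changes may occur during the treatment of rTMS". It also mentions a small possibility that rTMS provokes epilepsy, but does not list seizure among the rates. On Tui Na it says only: "In the process of Tui Na treatment, bone correction and other possible risk factors are not involved, and there is no serious risk".

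Under Research groups, both arms receive conventional rehabilitation and high-frequency rTMS. In the experimental arm, in addition, "the patients will receive Tui Na on the spine and hemiplegic side of UL".

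The Tui Na sections describe the component. On technique: "Kneading, pressing, one-finger meditation and active joint manipulations will be selected". On the intended sensation, for both the affected limb and the spine: "appropriate force will be used to make the patient feel sore and distended, and the treatment time is about 15 min". On precautions: "Closely observe the reaction of patients to timely adjust the amount of stimulation, and beware of adverse responses or accidents". The precautions section also mentions possible skin damage and provides for an accident during treatment.

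Table 1 has a general adverse event row, ticked at day 0, week 2, week 4 and the follow-up visit. The Safety analysis section plans a chi-square or exact test of the incidence of adverse events and adverse reactions between the two groups, without limiting it to the three named symptoms.

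**The concern.** A randomised comparison of adverse events informs mainly about what differs between the arms, and here that is Tui Na. The named outcomes were chosen for the component that is the same in both arms. For the component under test, the article states a conclusion about risk that the trial ought to be measuring.

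Two things are at stake. First, a report built on the named rates could find no difference in headache, vertigo and hearing changes and be read as reassurance about Tui Na, although no Tui Na harm was specified for collection. Second, soreness is an intended effect in one arm only. Without a rule, someone must decide later whether it is an adverse event, and that decision alone can change the result of the between-arm test.

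**Working it through.** The protocol gives no safety rate, safety power or safety sample size, so there is no stated figure to reproduce. The check is mainly a comparison of passages, with one calculation to size the soreness problem.

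**1. Named outcomes against the randomised difference**

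| Named rate | Source stated in the article | Arms exposed to that source |
|---|---|---|
| Headache | rTMS | both |
| Vertigo | rTMS | both |
| Hearing changes | rTMS | both |

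Named rates introduced for Tui Na: 0 of 3. Seizure is mentioned as an rTMS risk but is not a named rate.

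**2. Risk statement against the Tui Na instructions**

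The Adverse events paragraph says that possible risk factors are not involved and that serious risk is absent. The Matters-needing-attention section, written for the same treatment, tells the therapist to watch for adverse responses and accidents. An ordinary precaution does not prove a serious risk, so this is a tension and not a flat contradiction. It does show that the authors foresee Tui Na events, which makes their absence from the named rates harder to justify.

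**3. What the general provisions still capture**

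The word "including" is part of the sentence that introduces the three rates, so the list is not closed. Table 1 records adverse events generally, and the Safety analysis compares all of them. A Tui Na event that is recorded therefore enters the comparison.

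**4. Intended soreness in the all-event comparison**

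Inputs: 45 patients per arm recruited and 38 per arm required before dropout (Sample size calculation); two-sided Fisher's exact test at 0.05, as the exact option in the Safety analysis. Assumption for illustration: no other adverse events in either arm.

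For k events in the experimental arm and none in the control arm, with n per arm and k > 0, the two-sided p-value is 2 × C(n,k) / C(2n,k).

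| Experimental v control | p, 45 per arm | p, 38 per arm |
|---|---|---|
| 5 v 0 | 0.056 | 0.054 |
| 6 v 0 | 0.026 | 0.025 |

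So if intended soreness were recorded as an adverse event in 6 of 45 experimental patients (6/45 = 13%) and in no control patient, the planned test would be significant on soreness alone. The technique aims at soreness in every treated patient, so 6 is not a demanding number. The opposite choice, leaving out all soreness, would also leave out pain from a real injury.

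**5. How much the all-event test can show about Tui Na**

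Assumed true rates of an event that occurs only with Tui Na, against zero in control; power of the two-sided Fisher test at 0.05:

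| True rate | 45 per arm | 38 per arm |
|---|---|---|
| 5% | 2% | 1% |
| 10% | 29% | 18% |
| 15% | 69% | 52% |
| 20% | 91% | 80% |

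The test can register Tui Na harm, but only a large excess is likely to reach significance. Most of the safety information will therefore come from described rates of specified events, which is why the choice of named events matters.

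**The case against.** The strongest reply is that the general provisions already cover Tui Na: the list is open, Table 1 collects adverse events at four time points, the Safety analysis compares all of them, and a data monitoring committee supervises safety. This stands. A reader might infer that the safety comparison cannot answer for Tui Na at all, and the documents do not support that.

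A reader might also infer that Tui Na events would be counted only if patients volunteered them. Nothing says collection is passive, and therapists are told to observe reactions closely. How events are elicited is a detail that an article may leave to the full protocol and the case report form. However, that instruction to observe belongs to sessions that only one arm attends: 30 minutes in each of 20 sessions, or 600 minutes (10 hours). This favours asking the same questions in both arms.

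A third tempting reading is that the risk statement contradicts the exclusion criteria: "6) Patients with unstable or larger carotid plaques. (7) Patients with severe osteoporosis". The article gives no reason for these exclusions and does not tie them to Tui Na. Removing patients at higher risk is also compatible with low risk in those enrolled. That argument is not relied on here.

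Finally, it can be said that the sample size is the real limit on safety inference and that an event list does not change it. This is true of significance testing. It does not remove the case for specified, described rates, nor does it settle how soreness is counted.

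What remains is not missing detail. The article chose a list, gave its rationale and stated a conclusion about the tested component.

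**Conclusion.** The concern holds in a limited form. The named safety rates are aimed at the shared component (0 of 3 for Tui Na), the statement on Tui Na risk prejudges what the trial should observe and is in tension with the Tui Na precautions, and the all-event comparison is ambiguous because intended soreness arises in one arm only. The safety comparison is poorly targeted, not incapable of detecting a Tui Na event.

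The size rests on assumptions. The 6 v 0 result assumes no other events and the exact test; the power figures use assumed event rates, since the protocol gives none. They show that the handling of soreness can decide the test and that only large excesses would be significant. They do not measure how many Tui Na events general recording would miss, and the documents give no basis for estimating that. The point should be fixed. It does not affect the primary outcome.

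**What to change.** In the Adverse events section:

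- Remove the assertion that Tui Na carries no serious risk, or reconcile it with the Matters-needing-attention section.
- Add to the named rates a short list of Tui Na-related events, for example persistent local or shoulder pain, bruising or skin injury, joint injury or fracture, and neck-related vascular or neurological events. These are suggestions for the investigators to settle.
- Add seizure, which the section already mentions as an rTMS risk.
- Ask the same list in both arms at the Table 1 visits.

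In the Safety analysis section, state that intended soreness during the session is tabulated separately and does not enter the compared incidence, and define what separates it from pain recorded as an adverse event.

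The change concerns recording and reporting only; treatment and sample size stay as they are. It costs a few lines on the case report form and a wording change. The downside is a possibly higher event count in the experimental arm.
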